## LIST OF ABBREVIATIONS AND RELEVANT DEFINITIONS

|                |                                                                                                                                                                                                                                                                                                                                           |
|----------------|-------------------------------------------------------------------------------------------------------------------------------------------------------------------------------------------------------------------------------------------------------------------------------------------------------------------------------------------|
| ABR     | General Assessment and Registration form (ABR form), the application form that is required for submission to the accredited Ethics Committee; in Dutch: Algemeen Beoordelings- en Registratieformulier (ABR-formulier)                                                                                                                    |
| AE      | Adverse Event                                                                                                                                                                                                                                                                                                                             |
| AR      | Adverse Reaction                                                                                                                                                                                                                                                                                                                          |
| CA      | Competent Authority                                                                                                                                                                                                                                                                                                                       |
| CCMO    | Central Committee on Research Involving Human Subjects; in Dutch: Centrale Commissie Mensgebonden Onderzoek                                                                                                                                                                                                                               |
| CTG     | Cardiotocography                                                                                                                                                                                                                                                                                                                          |
| CV      | Curriculum Vitae                                                                                                                                                                                                                                                                                                                          |
| DSMB    | Data Safety Monitoring Board                                                                                                                                                                                                                                                                                                              |
| D-QUEST | Dutch version of the Quebec User Evaluation of Satisfaction with assistive Technology                                                                                                                                                                                                                                                     |
| DU      | Doppler Ultrasound                                                                                                                                                                                                                                                                                                                        |
| eCTG    | Electrophysiological cardiotocography                                                                                                                                                                                                                                                                                                     |
| EU      | European Union                                                                                                                                                                                                                                                                                                                            |
| GCP     | Good Clinical Practice                                                                                                                                                                                                                                                                                                                    |
| GDPR    | General Data Protection Regulation; in Dutch: Algemene Verordening Gegevensbescherming (AVG)                                                                                                                                                                                                                                              |
| HCP     | Healthcare professional                                                                                                                                                                                                                                                                                                                   |
| IB      | Investigator's Brochure                                                                                                                                                                                                                                                                                                                   |
| IC      | Informed Consent                                                                                                                                                                                                                                                                                                                          |
| METC    | Medical research ethics committee (MREC); in Dutch: medisch-ethische toetsingscommissie (METC)                                                                                                                                                                                                                                            |
| NFMS    | Nemo Fetal Monitoring System                                                                                                                                                                                                                                                                                                              |
| NI-fECG | Non-invasive fetal electrophysiological cardiography                                                                                                                                                                                                                                                                                      |
| NRM     | Nemo Remote® Monitoring                                                                                                                                                                                                                                                                                                                   |
| PIH     | Pregnancy induced hypertension                                                                                                                                                                                                                                                                                                            |
| PPQS    | Patient participation and satisfaction questionnaire                                                                                                                                                                                                                                                                                      |
| (S)AE   | (Serious) Adverse Event                                                                                                                                                                                                                                                                                                                   |
| Sponsor | The sponsor is the party that commissions the organisation or performance of the research, for example a pharmaceutical company, academic hospital, scientific organisation or investigator. A party that provides funding for a study but does not commission it is not regarded as the sponsor, but referred to as a subsidising party. |
| TOCO    | Tocodynamometry                                                                                                                                                                                                                                                                                                                           |
| UAVG    | Dutch Act on Implementation of the General Data Protection Regulation; in Dutch: Uitvoeringswet AVG                                                                                                                                                                                                                                       |
| US      | Ultrasound                                                                                                                                                                                                                                                                                                                                |
| VAS     | Visual analogue scale                                                                                                                                                                                                                                                                                                                     |
| WMO     | Medical Research Involving Human Subjects Act; in Dutch: Wet Medisch-wetenschappelijk Onderzoek met Mensen                                                                                                                                                                                                                                |

## SUMMARY

**Rationale:** Patients with obstetric complications like pre-eclampsia (PE), fetal growth restriction (FGR) or preterm pre-labor rupture of membranes (PPROM) often need hospitalization for fetal and maternal monitoring. Remote home monitoring has the potential to decrease the psychological and family burden of a hospital admission and to increase patient satisfaction while reducing health care costs due to a reduction in antenatal admissions. Previous research shows no indications that fetal home monitoring of selected complicated pregnancies imposes additional risks compared to in-hospital monitoring (1). Due to the limitations of conventional remote CTG monitoring like signal loss, electrophysiological cardiotocography (eCTG) has been developed and it is certified from 21 weeks of pregnancy onward. Since signal quality of eCTG in the preterm period – due to signal loss – is still unclear (2), the feasibility needs to be assessed first. The HASTA study will evaluate the feasibility of remote eCTG monitoring using non-invasive fetal electrocardiography (NI-fECG), Nemo Remote® Monitoring (NRM) in a hospital setting, as if the patient is at home (i.e., Home@Hospital setting). Automated interpretation of remote eCTG will be evaluated aiming to improve fetal monitoring and perinatal outcomes in the future. Additionally, this study will evaluate the feasibility of synchronized multimodal acquisitions of maternal and fetal measurements in a small population, aiming to understand the (patho)physiological mechanisms underlying cardiovascular function in pregnancy in the future.

**Objective:** To evaluate the feasibility of remote eCTG monitoring in complicated pregnancies between 32-37 weeks in a Home@Hospital setting. Secondary objectives are to evaluate automated interpretation of remote eCTG monitoring and to evaluate perinatal and maternal outcomes, patients and healthcare professionals satisfaction, and costs. Additional objective is to evaluate the feasibility of synchronized multimodal acquisitions of maternal and fetal measurements.

**Study design:** A single center interventional prospective cohort study.

**Study population:** Pregnant patients (N=60) >18 years old with a singleton, high-risk pregnancy from 32 until 37 weeks of gestational age. High-risk is defined as: diagnosed with PE, FGR, PPRM, or others with an indication for fetal monitoring at least twice a week, these patients are eligible for inclusion in this study. The main exclusion criteria are: suspected labor within 48 hours, severe pre-eclampsia, umbilical artery Doppler with absent- or reversed flow, external- or implanted electrical stimulator and language barrier.

**Intervention:** Remote eCTG monitoring (using Nemo Remote®), daily in a Home@Hospital setting for 30-90 minutes, or at least twice weekly at the outpatient clinic. Monitoring duration depends on signal quality and interpretability of the eCTG tracing, and lasts at least 30 minutes, and will be ceased after 90 minutes if the eCTG signal quality and/or interpretability is then still insufficient. In 24 patients ultrasound clips of 2 x 5 minutes of the uterine and umbilical artery Doppler will be collected simultaneously to the eCTG measurements.

**Main study parameters/endpoints:** Primary outcome: The percentage of successful eCTG measurements in a Home@Hospital setting. This will be defined as the necessity to switch to conventional CTG based on the amount of signal loss. Secondary outcomes: Automated interpretation of the eCTG, maternal and perinatal outcomes, patient and healthcare professional satisfaction and costs. Additional outcome: Feasibility of synchronized multimodal acquisitions of maternal and fetal measurements.

**Nature and extent of the burden and risks associated with participation, benefit and group**

**relatedness:** Participation in this study is expected not to cause any risk for the patient or fetus. In case eCTG registration is insufficient, a switch to the conventional CTG can be made.

The benefits of eCTG monitoring with Nemo Remote® include the fact that it is wireless, non-invasive and well positionable without the help of elastic belts. As a result, repetitive repositioning to reduce signal loss - as required when using conventional CTG frequently performed with the support of healthcare professionals (HCPs) - is not needed. This is beneficial for future implementation of home monitoring throughout pregnancy, thereby increasing the patient's autonomy. Conducting self-administered remote eCTG home monitoring in a hospital setting, enables the evaluation of the feasibility at home - most likely - without any risk to patient or fetus. Patients using Nemo Remote® have a very small – known and unrelated to remote monitoring – probability of developing skin irritation or a minor (local) allergic reaction to the skin electrodes from the abdominal patch. There is no need for treatment if skin irritation happens, as this will naturally resolve over the course of days once the patch is removed (as in NIEM-O W22.070, NIEM-II W22.071). Measurements of the umbilical- and uterine artery are widely applied in routine obstetric care and are known not to cause any harm to patient and/or fetus (3). At three moments participants will be asked to fill in digital questionnaires. All other interventions are standard care. No additional – study-related – hospital visits or fetal registrations are needed.

## 1. INTRODUCTION AND RATIONALE

### E-Health solutions

The use of digital health for remote monitoring in pregnancy care is increasingly popular (4). In complicated pregnancies, monitoring with cardiotocography (CTG) is recommended in international guidelines to assess maternal and fetal conditions resulting in recurrent outpatient visits or hospital admission (5-8). Antenatal admissions often pose psychological stress to pregnant women because of separation from family and home, lack of activity, and feelings of uncertainty (4). In general, digital health has the potential to improve access to care, thereby increasing patient satisfaction while reducing health care costs due to a reduction in visits and admissions (9, 10). Telemonitoring is a relatively new approach in complicated pregnancy and is recognized as an alternative to hospital admission (1, 9-11). Home monitoring in pregnancy can also attribute to the principal of family-integrated care (FIC) starting in pregnancy. Multiple telemonitoring platforms for remote CTG have been evaluated in prospective studies, and their feasibility and acceptability by patients and clinicians are proven (4). However, there are limitations in using conventional CTG equipment.

### Limitations of conventional remote CTG

The conventional CTG signals that are generated with Doppler Ultrasound (DU) and tocodynamometry (TOCO) are prone to signal artefacts and signal loss due to fetal and maternal movements, particularly in patients with a high body mass index (BMI) (12, 13). With an estimated prevalence of obesity of at least 12% (and at most 30%) of adults in the Netherlands in 2024, this is a common issue (14, 15). As a result of poor signal quality, the transducer often has to be repetitively repositioned (16) which complicates self-administered home monitoring. Additionally, loss of signal might be stressful for patients and patients experience the tightly fitted elastic bands as uncomfortable and this substantially limits their mobility (16).

### Remote electrophysiological cardiotocography monitoring (eCTG) – Nemo Remote® (NRM)

Due to the limitations of conventional CTG monitoring, extensive research has been carried out to develop new, non-invasive, monitoring methods. Remote eCTG – including NI-fECG – monitoring has shown to be a very promising technique (17-20). This technique uses a wireless and beltless electrode patch that is placed on the maternal abdomen (Figure 1). It monitors fetal heart rate (FHR) by fetal electrocardiography (fECG), maternal heart rate by maternal electrocardiography, and the electrical activity of the uterine muscle by electrohysterography (EHG) (21-24). The electrophysiological recordings are hardly affected by maternal or fetal movement or abdominal wall thickness, as they are transferred through conduction of electrical signals across the underlying tissues (13, 25). Furthermore, the wireless electrode patch on the maternal abdomen gives patients the ability to move (16). The HASTA study will evaluate the feasibility of self-administered home monitoring in a Home@Hospital setting for a selected groups of complicated pregnancies. Feasibility will be evaluated by assessing the success rate (percentage of successful measurements) of remote eCTG, and whether no switch to conventional CTG due to interpretability is needed. Success rate is defined as maximum of 20% signal loss of total recorded time or at least 30 minutes of sufficient CTG interpretability. For further description see sections 2.1 and 7.1.1.

[figure not shown][figure not shown]

*Figure 1. eCTG including NI-fECG – Nemo Remote® (NRM)*

Furthermore, the FHR obtained from the fetal ECG measurements collected through NRM in this study will be used to check if the algorithm of the FHR – developed during labor – can also benefit for premature fetus. Automated interpretation of fetal monitoring could lead to improved prevention in the future. In addition, the effects of self-administered remote eCTG monitoring in a Home@Hospital setting on maternal and perinatal outcomes, patient and HCP satisfaction, and costs will be evaluated.

Besides feasibility of eCTG, this study will additionally evaluate the feasibility of synchronized multimodal acquisitions of maternal and fetal measurements as a first step towards the development of a prediction model.

## **2. OBJECTIVES**

### **2.1 Primary objective**

The primary objective of this study is to assess the percentage of successful self-administered remote eCTG (including NI-fECG ) measurements in a Home@Hospital setting. This will be defined based on the percentage of signal loss and total duration of adequate registration and will be assessed on the first or – when indicated – the second eCTG measurement on the first day of inclusion. When the first remote eCTG measurement is reassuring but insufficient, the measurement will be repeated the same day.

### **2.2 Secondary objective(s)**

The secondary objective is to evaluate the interpretability of eCTG measurements throughout the hospital period as described in section 2.1 and defined in section 7.1.1. In addition – regarding eCTG measurements – will be assessed the number of repeated eCTG measurement the same day – because of insufficient interpretability – including possible causes of poor signal quality, and the number of switches from eCTG to conventional CTG including possible reasons. Furthermore, will be assessed automated interpretation and the effects of self-administered remote eCTG monitoring in a Home@Hospital setting on maternal and perinatal outcomes, patient and HCP satisfaction, and costs.

### **2.3 Additional objectives**

In addition, this study aims to evaluate the feasibility of synchronized multimodal acquisitions of maternal and fetal measurements to understand the (patho)physiological mechanisms underlying cardiovascular function in pregnancy. This is evaluated in a subset of 24 patients, where simultaneously with the eCTG measurements, Doppler US measurements of the umbilical and uterine arteries will be performed. In addition, automated interpretation of the – in this study collected – NI-fECG measurements through NRM will be evaluated, aiming to improve fetal monitoring, support the HCPs' interpretation and perinatal outcomes in the future.

### 3. STUDY DESIGN

The study will be conducted as a single center prospective cohort study between November 2024 and April 2026, aiming to include 60 eligible patients between 32 and 37 weeks of gestational age. The study is situated at the obstetric department of the Máxima Medical Center (MMC), a secondary and tertiary maternity care unit. However the aim of this study is to evaluate home monitoring in a hospital setting (Home@Hospital), only the use of remote eCTG through a NRM connection will differ from the standard care. A detailed description of the study population including sample size calculation, treatment of subjects, methods and statistical analysis, is provided in chapters 4,5,7 and 9. For study design and study procedures see Figure 2. The study will be registered on 'ToestingOnline' and 'www.clinicaltrials.gov'.

[figure not shown]

Figure 2. Flowchart of the HASTA prospective cohort design and study procedures.

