#### 7.1.2 Secondary study parameters

##### *Remote eCTG parameters*

- Number of days with remote monitoring per participant.
- Number of remote eCTG measurements per participant.
- Need to repeat remote measurements the same day because of reassuring but insufficient interpretability.
- Number of switch to conventional CTG and possible maternal and/or fetal reason.
- Number of switch to conventional CTG needed because of poor signal of remote eCTG measurement and possible cause.
- Success rate of CTG measurement after switch based on same criteria as in remote eCTG monitoring (7.1.1).
- Incidence of skin irritation.
- Number of “unscheduled visits” and reason.
  - When there is an indication for an additional visit in-hospital as if the participant is monitored at home (e.g. contractions, decreased fetal movements, PE symptoms, suspicion of PPRM).
- Number of “re-admissions” and reason.
  - When there is an indication of admission as if the participant is monitored at home (e.g. blood loss, threatened premature labor, hypertension with indication for intravenous medication).
- The number of eCTG measurements assessed successful at closure by HCP.
- The number of eCTG measurements prematurely closed by HCP before complying the criteria of a successful measurement (7.1.1).

- Maternal and fetal factors HCPs have included in their assessment of the eCTG measurement (e.g. GA, fetal growth, Doppler measurements, PPRM).

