## **8. SAFETY REPORTING**

### **8.1 Temporary halt for reasons of subject safety**

In accordance to section 10, subsection 4, of the WMO, the sponsor will suspend the study if there is sufficient ground that continuation of the study will jeopardise subject health or safety. The sponsor will notify the accredited METC without undue delay of a temporary halt including the reason for such an action. The study will be suspended pending a further positive decision by the accredited METC. The investigator will take care that all subjects are kept informed.

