### **8.2 AEs, SAEs and SUSARs**

#### **8.2.1 Adverse events (AEs)**

Adverse events are defined as any undesirable experience occurring to a subject during the study, whether or not considered related to the investigational product (e.g. skin irritation or minor (local) allergic reaction occurring within twelve hours after removal of the investigational product). All adverse events reported spontaneously by the subject or observed by the investigator or his staff will be recorded.

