#### **8.2.2 Serious adverse events (SAEs)**

A serious adverse event is any untoward medical occurrence or effect that:

- Results in death;
- Is life threatening (at the time of the event);
- Requires hospitalization or prolongation of existing inpatients' hospitalization;
- Results in persistent or significant disability or incapacity;
- Is a congenital anomaly or birth defect; or
- Any other important medical event that did not result in any of the outcomes listed above due to medical or surgical intervention but could have been based upon appropriate judgement by the investigator.

An elective hospital admission will not be considered as a serious adverse event.

The investigator will report all SAEs, that occurred during hospitalization from application until twelve hours after removal of the investigational product, to the sponsor without undue delay after obtaining knowledge of the events:

- Maternal or fetal death for any reason;
- Severe allergic reaction of abdominal patch or application technique that requires hospitalization or prolongation of existing inpatients hospitalization;
- Any unforeseen important medical event as a result of the investigational product that needs medical intervention.

The investigator will report all SAEs to the sponsor without undue delay after obtaining knowledge of the events, except for the following SAEs:

- SAEs or AEs that did occur independently from the investigational product, but as a consequence of a (pregnancy or delivery related) disease, will not be reported to the sponsor. For example, criteria described by neonatal and maternal morbidity, shoulder dystocia, known congenital anomaly or birth defect, dysmaturity, macrosomia, hypoglycaemia, hyperbilirubinemia, feeding problem/weight loss, therapeutic hypothermia, perinatal asphyxia, observation for meconium-stained amniotic fluid, observation for suspected infection, because of maternal medication use in pregnancy, maternal intrapartum fever or maternal hypertensive disorders.
- The Investigator will report the SAEs through the web portal 'ToetsingOnline' to the accredited METC that approved the protocol, within 7 days of first knowledge for SAEs that result in death or are life threatening followed by a period of maximum of 8 days to complete the initial preliminary report. All other SAEs will be reported within a period of maximum 15 days after the sponsor has first knowledge of the serious adverse events.

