#### **8.2.3 Follow-up of adverse events**

All AEs will be followed until they have abated, or until a stable situation has been reached.

Depending on the event, follow up may require additional tests or medical procedures as indicated, and/or referral to the general physician or a medical specialist.

SAEs need to be reported till end of study within the Netherlands, as defined in the protocol.

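### Self-measured vital signs with Luscii registration are an unnamed departure from standard care; separately, the SAE rules in 8.2.2 test causality against the device and no other study procedure

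*Protocol*

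**What the plan says.** **Departure from standard care.** Protocol section 3 says that "only the use of remote eCTG through a NRM connection will differ from the standard care". The burden and risk paragraph of the Summary mentions the Doppler measurements and the questionnaires and then classes every other intervention as standard care. Section 10.4 mentions the Doppler and classes the rest as routine.

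**SAE reporting.** Section 8.2.2 has two reporting statements.

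- The first is a short list that applies in hospital, in a window that opens when the device is applied and closes twelve hours after it is taken off. It covers maternal or fetal death from any cause, severe allergic reaction to the patch or its application, and a catch-all for unforeseen important events resulting from the investigational product.
- The second carries no window: "The investigator will report all SAEs to the sponsor without undue delay after obtaining knowledge of the events, except for the following SAEs". The exempt SAEs are those that "occur independently from the investigational product, but as a consequence of a (pregnancy or delivery related) disease, will not be reported to the sponsor". The examples begin with "criteria described by neonatal and maternal morbidity".

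Section 8.2.3 adds that "SAEs need to be reported till end of study within the Netherlands, as defined in the protocol".

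**Who acts on the reports.** Under 8.1 "the sponsor will suspend the study if there is sufficient ground that continuation of the study will jeopardise subject health or safety". Section 8.2.4 marks a DSMB as not applicable.

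**The concern.** There are two separate points.

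First, the statements meant to tell an ethics committee what the study changes are incomplete. In a population that includes pre-eclampsia and PPROM, who takes the blood pressure and temperature is a change that belongs in the risk statement.

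Second, the only study element whose causal role 8.2.2 asks about is the device. The study replaces staff measurement with self-measurement and adds Doppler clips in 24 participants, but neither SAE statement asks whether those procedures contributed to an event. An SAE to which a study procedure contributed is one the sponsor should receive, because the sponsor decides on a halt and no DSMB stands behind that decision. As worded, such an event can be left out of SAE reporting.

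**Working it through.** No figure in the plan bears on this point, so the check is a comparison of texts.

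**Step 1: is the eCTG the only change?**

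| Element | Standard care | Study participants |
|---|---|---|
| Fetal monitoring | Conventional CTG (5, 7.3.1) | Self-administered remote eCTG (5.1) |
| Vital signs | Collected as part of routine hospital care (5.1); measurements done by staff (7.3.1) | Taken by the participant, inpatient and outpatient (5.1, 7.3.2) |
| Symptoms and readings in Luscii | Not registered by the patient (7.3.1) | Registered at every eCTG measurement (5.1, 7.3.2) |
| Simultaneous Doppler clips | Not described as part of standard monitoring | Offered to 24 participants (2.3, 5.1) |

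The second and third rows differ for all 60 participants, so the section 3 sentence is wrong. The Summary and 10.4 pick up the fourth row but not the second and third. The caption of Figure 12 lists Luscii among the study interventions. That is only supporting evidence, since it lists the questionnaires there as well.

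**Step 2: what is the investigational product?** Section 6.1 names the Nemo Remote, and 6.4.3 gives its parts as the Link, the charger and the app. Its intended use covers fetal heart rate, uterine activity and maternal heart rate. It does not cover blood pressure or temperature. For outpatients, 7.3.2 says the blood pressure monitor and thermometer come from a self-measurement kit.

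**Step 3: take one hypothetical event through 8.2.2.** Suppose a participant has non-fatal eclampsia, and a wrong or late self-taken blood pressure reading delayed its recognition.

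1. Windowed list, death: no.
2. Windowed list, severe allergic reaction: no.
3. Windowed list, catch-all: no, because the event did not result from the product.
4. General rule: report, unless exempt.
5. Exemption, first condition (independent of the product): met, because the blood pressure monitor is not part of the Nemo Remote.
6. Exemption, second condition (consequence of a pregnancy- or delivery-related disease): met on a literal reading.
7. Examples: maternal morbidity is named, and 7.1.2 lists eclampsia, HELLP, abruption and chorioamnionitis under that term.

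The event can therefore be read as exempt. Nothing in steps 1 to 7 asks whether a study procedure contributed.

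**Step 4: where would the event still appear?** Section 8.2.1 defines adverse events "whether or not considered related to the investigational product" and has those reported or observed recorded. Section 7.1.2 collects maternal morbidity. It also collects unscheduled visits and re-admissions with their reasons; one example of a re-admission reason is "hypertension with indication for intravenous medication". The gap is therefore in SAE reporting to the sponsor, not in data collection.

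**The case against.** The strongest reply has five parts.

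- **The exemption has two conditions.** A reader might infer that it asks only about independence from the device. It does not: the event must also be a consequence of pregnancy- or delivery-related disease. An investigator could fairly say that an event made worse by a failed study measurement is not simply a consequence of disease, and report it under the general rule. This stands, and it is why the event can be read as exempt rather than must be. Deaths within the window are on the reporting list whatever their cause.
- **The two points are not shown to be linked.** A reader might infer that the omission in section 3 produced the wording of 8.2.2. The documents do not support that. The exemption also leaves out the Doppler, which the Summary and 10.4 do disclose. The points should be treated separately.
- **No added risk is shown.** A reader might infer that self-measurement endangers participants. The documents point the other way. Measurements take place in hospital or at the clinic; staff watch the trace, transfer the Luscii entries, telephone the participant and visit inpatients (7.3.2). This stands.
- **Luscii is already in regular use at the centre (5.1).** This makes it less novel, but does not remove the contradiction: 7.3.1 says that patients under standard care do not register in it, and the remark does not bear on who takes the readings.
- **Section 3 is an overview.** Chapters 5 and 7 describe self-measurement consistently, so staff are unlikely to be misled. That is fair for conduct, but it does not correct the risk statements in the Summary and 10.4.

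Sections 11.4 and 11.5 join the sponsor and investigator roles in one term, which may mean that the two sit close together. The removed title pages leave this open, and it does not repair the rule.

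**Conclusion.** The contradiction about standard care is definite and concerns all 60 participants. The SAE gap is real but narrow: it covers non-fatal SAEs that are independent of the Nemo Remote, follow from pregnancy- or delivery-related disease, and were contributed to by self-measurement, Luscii registration or the Doppler add-on. Such events can be read as exempt from reporting to the sponsor, though they would still be captured as adverse events or outcomes.

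The number of such events cannot be estimated. The documents give no rate for them or for self-measurement failure, and the number may be zero. Counting how many listed morbidities have warning signs among the self-measured items would rest on clinical assumption and would not measure the gap.

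The conclusion on reporting rests on a literal reading of the exemption, which an investigator could apply more protectively. The primary outcome and sample size are unaffected. This is a minor-to-moderate safety-reporting correction, worth making because it costs little.

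**What to change.** 1. In 8.2.2, extend the first condition of the exemption so that the event must be independent of the investigational product *and of study procedures*, naming self-measurement, Luscii registration and the Doppler add-on.
2. In the windowed list of 8.2.2, extend the catch-all to events resulting from the product *or a study procedure*. Without this, the first change has no effect if the list is taken as the governing rule.
3. In the Summary, section 3 and 10.4, name self-measured vital signs with Luscii registration as a departure from standard care.

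**Cost:** two clauses and three short wording corrections. Each otherwise exempt SAE needs one extra causality question, and a few more reports may follow. SAEs due to disease alone stay exempt.
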